### Consent process

During the consent process, potential participants and their approved carers will be provided with all pertinent information, including information regarding any associated sub-studies by the research staff. This information will be in the form of a participant information sheet (PICF) and will be supported by offers of verbal clarification of any additional queries. The purpose, expected procedures, participant requirements, benefits, risks, burdens and anticipated or possible adverse effects will be covered by this process. Participants will be explicitly reminded they cannot drive or operate heavy machinery nor take any non-trial cannabinoid products whilst taking the trial medication.

Potential participants will be given as much time and space as is necessary to formulate any questions and come to a decision. Any questions will be addressed. The consent form will be completed by a study team member in accordance with ethics committee requirements. The form will be signed and dated by the participant and investigator.

There will be separate consent forms for the RCT and the sleep sub-study. Patients will only be able to participate (optionally) in the sleep sub-study component if they consent to the main RCT.

### Randomisation

Eligible patients will be assigned in equal numbers to one of the two arms at random. Random number tables will be used for computer-generated randomisation schedules at an independent location by the staff not otherwise involved in the trial. A central registry will hold treatment allocations as determined by a permuted block randomisation schedule. Each site will have its own block randomisation schedule leading to even allocation to each treatment arm within each site. Actions to minimise the risk of bias are detailed in Additional file 1: Table S1.

Following fully informed written consent, the procedure will be as follows:The research pharmacy will be notified of a new participant.The investigator will complete a trial prescription with the participant’s study ID number and provide this to the trial pharmacy.Based on the randomisation schedule, the pharmacist will dispense the appropriate medication in a bottle labelled ‘THC:CBD 10 mg:200 mg/mL or placebo’.Participant ID, allocation number, date of request, preparation and dispensing will be recorded by the site pharmacist for each instance.

### Intervention

Trial medication and placebo oil formulation will be provided by Little Green Pharma Ltd. Little Green Pharma is supplying the medication free of charge but has no input into the study design nor execution. They will have no role in the analysis or publication of results.

The intervention arm (arm 1) is an oil formulation of THC/CBD 10 mg/200 mg/mL for oral administration (LG Pharma Pty Ltd.) to be delivered over the dose range of THC:CBD 2.5 mg/50 mg (0.25 mL once daily) to THC:CBD 30 mg/600 mg per day (1 mL three times daily). The placebo (arm 2) is a taste and appearance-matched oil formulation without the active ingredient though otherwise indistinguishable. Both arms will otherwise receive the usual palliative care. No part of usual palliative care is prohibited as part of the trial.

Both active and placebo arms will be provided one 70-mL bottle containing 50 mL of the oil solution. Participants will be instructed to store the bottles at room temperature and away from light. Bottles will have a child-resistant cap. Participants will be educated about how to administer medication via a supplied syringe and how to follow the dosing schedule. They will be instructed to use only those syringes supplied by investigators. Participants will record their dosing in the provided dosing schedule diary. Any product remaining at the conclusion of the trial will be returned to the research officer and destroyed by the local site pharmacy in accordance with pharmacy guidelines. Participants who are enrolled through the teletrial infrastructure will have their trial medicine sent to their local Queensland Health (government) facility for safekeeping until they retrieve it. They will use it in a similar way and then return it to the facility at the end of the trial.

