#### Study design

This is a pragmatic, multicentre, randomised, placebo-controlled, two-arm parallel trial of escalating doses of oral THC/CBD: 10 mg:200 mg/mL oral solution. Participants will self-titrate the dose over the first 14 days using a pre-defined dosing schedule. They will cease self-titration at the maximum day 14 dose or at that dose which relieves symptoms or is limited by adverse effects. This dose will be continued for a further 2-week period for documentation of any benefits and adverse effects. This study design is based on previous RCTs successfully undertaken by this group [3, 4, 7].

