#### Dose titration

Dose titration will be in accordance with the dosing schedule starting at 0.25 mL once daily. The dose increases every 2 days until the participant is satisfied with symptom improvement, experiences adverse events that are not acceptable or reaches the maximum dose (at the end of the 14-day dose-titration phase). Participants will be reviewed by phone or in person two to three times per week during this phase. If participants are reluctant to increase their dose because of adverse effects, they can consult with the research staff and maintain the current dose or reduce the dose or dosing frequency. All deviations from the dosing schedule will be recorded by the research staff. Detection of unexpected deviation is aided by comparing the volume remaining with the expected volume remaining for that time point. Exceeding the maximum dose as specified in the dosing schedule is not permitted.

Participants will be given the opportunity to remain on their chosen dose for an additional 14 days (a total of 28 days) to monitor ongoing efficacy and adverse events.

Participants consenting to the sleep study will be provided with an accelerometer to be worn nightly for the duration of the sub-study.

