Secondary outcomes include the following:Patient-determined effective dose of THC/CBD 1:20 formulation, defined as the dose that achieves symptom relief with acceptable side effects.ESAS TSDS at days 7, 21 and 28.Physical and emotional ESAS scores at each time point.Physical scores will be measured by the AKPS and Resource Utilisation Groups-Activities of Daily Living Scale (RUG-ADL). The AKPS is a validated variant of the Karnofsky Performance Status [11]. The Australian version can be applied to both inpatients and outpatients and is sensitive to changes in function over time. The RUG-ADL is an instrument developed for the measurement of nursing dependency [12]. The ADL scale measures patients’ needs for assistance in activities of daily living (eating, bed mobility, transferring and toileting).Individual symptom scores (descriptive analysis only).Oral morphine equivalent (OME), average use at baseline and weekly.Patient Global Impression of Change (PGIC), days 7, 14, 21 and 28.This is a subjective measure of symptom change completed by the participants themselves [13].Clinical Global Impressions (CGI) scale, days 7, 14, 21 and 28.This is a subjective measure of symptom change completed by the investigating clinician [13].The Depression, Anxiety and Stress Scale (DASS-21).DASS-21 is a self-reported 21-item scale, 7 questions per sub-item questionnaire measuring depression, anxiety and stress [14]. The DASS-21 will be used for assessment at baseline (day 0) and at days 14 and 28.EORTC score QoL baseline and days 14 and 28.This is a QoL measure found valid for use in a wide variety of cancer populations. To reduce patient burden, we will use the 15-question subset commonly used for the palliative care population [13].NCI common terminology for adverse events V4.03, days 2, 4, 7, 9, 11, 14, 16, 18, 21, 23, 25 and 28.The NCI CTCAE is a severity grading system for adverse events [15]. Adverse events relate to an unfavourable or unintended sign, symptom or disease temporarily associated with a medical treatment or a procedure which may not be related to the medical treatment or procedure. The CTCAE has a grading of 1 (mild) to 5 (death). The known common adverse events associated with cannabinoids are confusion, somnolence, paranoia, anxiety, mood changes, psychosis, hypertension, tachycardia, hyperhidrosis, nausea, vomiting and abdominal pain.The study will assess adverse events (AE) and serious adverse events (SAE) using the criteria of the NCI CTCAE V4.0. The known common AEs associated with THC/CBD will be sought at each time point. A comprehensive clinical review which includes the compilation of a concurrent medication list will occur at days 0, 7, 14, 21 and 28. This will include over-the-counter and complementary medications in addition to prescribed medications.SleepESAS (with additional sleep score item) at days 0, 7 and 14.Objective measure of sleep via actigraphy. These measures will include total sleep time, sleep efficiency, wake after sleep onset and sleep onset latency (min). Participants will wear an accelerometer on their wrists for 14 days to measure circadian activity, sleep quality and quantity. Actigraphy has been found to be a validated, objective way to measure sleep outcomes [8].The ISI is a measurement tool that assesses sleep quality. It consists of 7 questions each of which are scored 0 (best) to 4 (worst) with respect to sleep quality [16]. Interpretation is by the total score which classifies 0–7 as no clinically significant insomnia, 8–14 as subthreshold insomnia, 15–21 as clinical insomnia of moderate severity and 22–28 as severe clinical insomnia. The Sleep Numerical Score is an 11-point numerical rating scale where 0 is the best possible sleep, and 10 is the worst possible sleep.

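### As written, one 50 mL bottle does not cover 28 days for a participant who titrates to 3 mL/day on any ordinary stepwise schedule

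*Protocol article*

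**What the plan says.** All statements are in the protocol article.

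- **Supply (Intervention):** "Both active and placebo arms will be provided one 70-mL bottle containing 50 mL of the oil solution". No section mentions a second bottle.
- **Maximum dose (Intervention):** "THC:CBD 30 mg/600 mg per day (1 mL three times daily", which is 3 mL/day.
- **Titration (Dose titration):** dosing starts at 0.25 mL once daily and goes up every 2 days. It stops at satisfactory relief, at unacceptable adverse effects, or when the participant "reaches the maximum dose (at the end of the 14-day dose-titration phase". Study design puts it as "They will cease self-titration at the maximum day 14 dose".
- **Continuation:** Study design says "This dose will be continued for a further 2-week period". Dose titration says "Participants will be given the opportunity to remain on their chosen dose for an additional 14 days (a total of 28 days".
- **Volume check (Dose titration):** unexpected dosing deviations are detected by "comparing the volume remaining with the expected volume remaining for that time point".
- **Late measurements (Outcomes and assessment tools):** several secondary outcomes are measured at day 28, and adverse events are graded on "days 2, 4, 7, 9, 11, 14, 16, 18, 21, 23, 25 and 28".

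**The concern.** The supply, the maximum dose and the length of dosing are all stated, so they can be set against each other, and at the top dose they do not fit. The second fortnight alone takes 42 of the 50 mL. A participant who follows the plan to the maximum could therefore be without study oil, or on an unplanned lower dose, before the day-28 visit.

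At stake are the day-28 secondary outcomes (TSDS, PGIC, CGI, DASS-21 and EORTC quality of life) and the latest adverse-event contacts. The loss would fall on participants with the highest exposure, for whom the second fortnight's safety information matters most.

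**Working it through.** **Inputs.** Supply 50 mL; maximum 1 mL three times daily; concentration 10 mg THC and 200 mg CBD per mL (all Intervention). Start 0.25 mL/day, a rise every 2 days, 14 days of titration, then 14 days at the chosen dose (Dose titration).

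**Stated maximum reproduced.** 30/10 = 600/200 = 3 mL/day, which agrees with 1 mL three times daily.

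**Fixed-dose phase.** Days 15-28: 14 × 3 = 42 mL. Left for titration: 50 − 42 = 8 mL, and 8/14 = 0.57 mL/day.

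**Lower bounds that need no dosing table**, holding 0.25 mL/day until the maximum:

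- 3 mL/day from day 13: 12 × 0.25 + 16 × 3 = 51 mL (over 50)
- 3 mL/day from day 14: 13 × 0.25 + 15 × 3 = 48.25 mL (under 50)
- 3 mL/day from day 15: 14 × 0.25 + 14 × 3 = 45.5 mL (under 50)

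The last two fit only because the dose never rises during titration, which contradicts a rise every 2 days.

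**Bounds with rises every 2 days** (step size assumed):

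- Rises of 0.25 mL, 3 mL/day from day 15: 2 × (0.25 + 0.50 + … + 1.75) + 42 = 14 + 42 = 56 mL
- Rises of 0.25 mL, 3 mL/day from day 13: 2 × (0.25 + … + 1.50) + 6 + 42 = 10.5 + 48 = 58.5 mL
- Rises of 0.10 mL, 3 mL/day from day 15: 2 × (0.25 + 0.35 + … + 0.85) + 42 = 7.7 + 42 = 49.7 mL. This fits, but only with a jump from 0.85 to 3 mL/day.
- Rises of 0.05 mL, 3 mL/day from day 15: 47.6 mL, with a larger jump.

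**Five assumed schedules**, each with seven 2-day steps. Total = titration + 42. Last full day = 14 + the whole number of 3 mL days in the volume left after day 14.

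| Schedule (mL/day) | Days 1-14 (mL) | Total (mL) | Short by (mL) | Left after day 14 (mL) | Left after day 21 (mL) | Last full day |
|---|---|---|---|---|---|---|
| A: 0.25, 0.36, 0.51, 0.72, 1.03, 1.48, 2.10; 3 from day 15 | 12.9 | 54.9 | 4.9 | 37.1 | 16.1 | 26 |
| B: 0.25 to 1.75 by 0.25; 3 from day 15 | 14 | 56 | 6 | 36 | 15 | 26 |
| C: 0.25 to 1.50 by 0.25; 3 from day 13 | 16.5 | 58.5 | 8.5 | 33.5 | 12.5 | 25 |
| D: equal steps, 0.25 to 3 | 22.75 | 64.75 | 14.75 | 27.25 | 6.25 | 23 |
| E: 0.25, 0.75, 1.25, 1.75, 2.25, 2.75, 3 | 24 | 66 | 16 | 26 | 5 | 22 |

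The first short day is 27, 27, 26, 24 and 23. The day-28 contact is exposed in all five schedules, day 25 only in D and E, and day 23 only in E.

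**Lower chosen doses, same schedules.** Stopped at 2.5 mL/day, the need is 47.9, 49, 50.5, 56.7 and 57.5 mL: enough in A and B, short in C, D and E (last full day 27, 25, 25). Stopped at 2 mL/day, it is 40.7, 42, 42.5, 47.5 and 48 mL: enough in all five.

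**What is not touched.** Titration cannot exceed 14 × 3 = 42 mL, so day 14 is always supplied. In all five schedules oil remains after day 21.

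**The case against.** **Resupply may be in the full protocol.** An article often leaves pharmacy logistics to the full document. This one does not say that the single bottle must last 28 days. Intervention uses the plural for bottles when it describes storage, and Randomisation has the pharmacist log every dispensing; both leave room for a repeat. Both also fit one bottle each across many participants, and neither states a second bottle. The objection stands to this extent: running out is conditional on there being no resupply. It does not remove the conflict, because the article gives a number of bottles, and that number does not fit the dosing.

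**The 51 mL floor is conditional.** A reader might take it as holding under any titration. It needs 3 mL/day by day 13. If the first dose is taken at the day-0 visit, 2-day steps bring the maximum in on day 14 of that count, after 14 full titration days, and the absolute floor is 45.5 mL. This stands. The shortfall then rests on assumed step sizes, although only a schedule that stays very low and makes most of its climb at the very end would fit.

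**Continuation is optional and volume is watched.** The second fortnight is offered, not required. But one bottle cannot honour the offer at the top dose, and the day-56 contact, placed 4 weeks after the last dose, presumes dosing to day 28. The volume check and the day-14 and day-21 reviews would show a low bottle, but they supply no oil.

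**The reach is narrow.** This stands. Titration stops at relief or intolerance, and the share of participants near 3 mL/day is not given.

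**Conclusion.** The point holds as an inconsistency between stated supply and stated dosing. A participant at 3 mL/day to day 28 needs at least 51 mL if the maximum is in force by day 13. The need is at least 56 mL if the maximum starts on day 15 after rises of 0.25 mL or more. The five assumed schedules fall short by 4.9 to 16 mL.

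This rests on two assumptions: ordinary step sizes, because the dosing table is not shown, and no resupply in the full protocol. On those assumptions, top-dose participants first run short on about days 23-27.

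A reader might infer more than the article supports:

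- That the trial's main result is at risk. It is not: the day-14 primary outcome, the day-7 and day-21 outcomes and the sleep sub-study (days 0-14) are all supplied.
- That the day-23 and day-25 adverse-event contacts are generally lost. They are exposed only under the steeper schedules.
- That many participants are affected, or more in one arm. The article gives no figure for either.

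**What to change.** At the day-14 visit, dispense a second bottle of the same allocation to anyone whose chosen daily dose × 14 exceeds the volume remaining. Apply the same rule in both arms; it depends only on dose and volume, so it does not reveal allocation. Remaining volume is already compared with expected volume, so the trigger needs no new measurement. If the full protocol already allows resupply, correct the article's statement of one bottle.

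Anyone who still runs out should stay in the day-28 analysis as randomised, with the last dose read from the dosing diary.

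The cost is one sentence, one extra bottle, and one dispensing or courier step for high-dose participants. In the five schedules at least 26 mL remains after day 14, which is 8 full days at 3 mL/day and leaves time to reach teletrial participants.

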#### Dose titration

Dose titration will be in accordance with the dosing schedule starting at 0.25 mL once daily. The dose increases every 2 days until the participant is satisfied with symptom improvement, experiences adverse events that are not acceptable or reaches the maximum dose (at the end of the 14-day dose-titration phase). Participants will be reviewed by phone or in person two to three times per week during this phase. If participants are reluctant to increase their dose because of adverse effects, they can consult with the research staff and maintain the current dose or reduce the dose or dosing frequency. All deviations from the dosing schedule will be recorded by the research staff. Detection of unexpected deviation is aided by comparing the volume remaining with the expected volume remaining for that time point. Exceeding the maximum dose as specified in the dosing schedule is not permitted.

Participants will be given the opportunity to remain on their chosen dose for an additional 14 days (a total of 28 days) to monitor ongoing efficacy and adverse events.

Participants consenting to the sleep study will be provided with an accelerometer to be worn nightly for the duration of the sub-study.

### Assessments

The research staff will contact all participants twice weekly for the first 2 weeks in addition to outpatient clinic reviews on days 0, 7, 14, 21 and 28, with outcome measures recorded at each of these time points. In addition to clinical documentation, symptom burden will be assessed using the Edmonton Symptom Assessment Scale (ESAS). Documentation of disease status (e.g. response or progression of disease) will be assessed at days 14 and 28.

A routine haematology and biochemistry screen including liver function tests will be taken at eligibility/baseline assessment. Blood for C-reactive protein (CRP) as a basic test of inflammation will be taken at baseline, day 14 and day 28. All consenting participants will have a urine test to confirm no recent use of THC-related products as a pre-screen. Female participants of child-bearing potential will have a urine test to exclude pregnancy. Additionally, patients will receive a phone call from a research nurse twice per week in the first fortnight, and then once per week for the second fortnight. Adverse events will be assessed at all of these interactions.

Participants in the optional sleep sub-study will be assessed using the Insomnia Severity Index (ISI) and Sleep Numerical Scale at days 0, 7 and 14. They will wear an accelerometer on their wrists for 14 days to measure circadian activity, sleep quality and quantity. Actigraphy has been found to be a validated, objective way to measure sleep outcomes [8].

Participants will be contacted at day 56 (+ 4 weeks post-last dose) to assess for adverse events as well as record post-trial cannabinoid use. Death will be noted for all participants up to the census point. This protocol has been written in accordance with the Standard Protocol Items: Recommendations for Interventional Trials (SPIRIT) (Table 1) [9]. A SPIRIT guideline checklist can be found in the supplementary material.

**Table 1 Tab1:**
[figure not shown]
Study schedule

^*^Only those women of reproductive potential

^**^Confirm documented disease status

^****^CADSS only if indicated during adverse event assessment

^Including complementary medicine use

^#^Eligibility data to be used as a baseline as long as within 3 days of each other

^«^Day 7 and 21 review may be conducted via telehealth if deemed appropriate

^=^Optional sleep secondary aim 1 only—days 0–14

### Outcomes and assessment tools

The primary outcome is the change from the baseline of total ESAS TSDS at day 14. The ESAS is a nine-item inventory rated on an 11-point scale anchored at 0 (no problem) to 10 (worst imaginable of this problem). It assesses both physical and psychological symptoms, plus general well-being [6]. It has been validated in the assessment of symptoms in cancer patients [10].

Secondary outcomes include the following:Patient-determined effective dose of THC/CBD 1:20 formulation, defined as the dose that achieves symptom relief with acceptable side effects.ESAS TSDS at days 7, 21 and 28.Physical and emotional ESAS scores at each time point.Physical scores will be measured by the AKPS and Resource Utilisation Groups-Activities of Daily Living Scale (RUG-ADL). The AKPS is a validated variant of the Karnofsky Performance Status [11]. The Australian version can be applied to both inpatients and outpatients and is sensitive to changes in function over time. The RUG-ADL is an instrument developed for the measurement of nursing dependency [12]. The ADL scale measures patients’ needs for assistance in activities of daily living (eating, bed mobility, transferring and toileting).Individual symptom scores (descriptive analysis only).Oral morphine equivalent (OME), average use at baseline and weekly.Patient Global Impression of Change (PGIC), days 7, 14, 21 and 28.This is a subjective measure of symptom change completed by the participants themselves [13].Clinical Global Impressions (CGI) scale, days 7, 14, 21 and 28.This is a subjective measure of symptom change completed by the investigating clinician [13].The Depression, Anxiety and Stress Scale (DASS-21).DASS-21 is a self-reported 21-item scale, 7 questions per sub-item questionnaire measuring depression, anxiety and stress [14]. The DASS-21 will be used for assessment at baseline (day 0) and at days 14 and 28.EORTC score QoL baseline and days 14 and 28.This is a QoL measure found valid for use in a wide variety of cancer populations. To reduce patient burden, we will use the 15-question subset commonly used for the palliative care population [13].NCI common terminology for adverse events V4.03, days 2, 4, 7, 9, 11, 14, 16, 18, 21, 23, 25 and 28.The NCI CTCAE is a severity grading system for adverse events [15]. Adverse events relate to an unfavourable or unintended sign, symptom or disease temporarily associated with a medical treatment or a procedure which may not be related to the medical treatment or procedure. The CTCAE has a grading of 1 (mild) to 5 (death). The known common adverse events associated with cannabinoids are confusion, somnolence, paranoia, anxiety, mood changes, psychosis, hypertension, tachycardia, hyperhidrosis, nausea, vomiting and abdominal pain.The study will assess adverse events (AE) and serious adverse events (SAE) using the criteria of the NCI CTCAE V4.0. The known common AEs associated with THC/CBD will be sought at each time point. A comprehensive clinical review which includes the compilation of a concurrent medication list will occur at days 0, 7, 14, 21 and 28. This will include over-the-counter and complementary medications in addition to prescribed medications.SleepESAS (with additional sleep score item) at days 0, 7 and 14.Objective measure of sleep via actigraphy. These measures will include total sleep time, sleep efficiency, wake after sleep onset and sleep onset latency (min). Participants will wear an accelerometer on their wrists for 14 days to measure circadian activity, sleep quality and quantity. Actigraphy has been found to be a validated, objective way to measure sleep outcomes [8].The ISI is a measurement tool that assesses sleep quality. It consists of 7 questions each of which are scored 0 (best) to 4 (worst) with respect to sleep quality [16]. Interpretation is by the total score which classifies 0–7 as no clinically significant insomnia, 8–14 as subthreshold insomnia, 15–21 as clinical insomnia of moderate severity and 22–28 as severe clinical insomnia. The Sleep Numerical Score is an 11-point numerical rating scale where 0 is the best possible sleep, and 10 is the worst possible sleep.
